### Outcome measures

The study period is 16 weeks. FMA-UE, MAS, ARAT, ADL, and fMRI will be assessed before and after the treatment, as well as safety indicators such as blood routine test, urine routine test, stool routine test, liver and kidney function examination, and blood glucose. All the patients will take FMA-UE, MAS, ARAT, and ADL assesses after 12 weeks follow-up. Health economic indicators were recorded at week 4 and week 16. All outcomes will be measured by several experienced assessors who are blinded to the randomization group after the baseline visit for evaluation. All assessors will be trained to administer these assessments.

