#### Primary outcomes

The primary outcomes in this study are the mean change in the scores on the FMA-UE from baseline to 4 weeks intervention and 12 weeks follow-up, as well as fMRI between the two groups and within groups from baseline to 4 weeks intervention.

FMA-UE is widely used for motor function assessment and can reflect the functional level of stroke subjects. The upper extremity has a maximum score of 66 points divided into three parts, namely shoulder arm (36 points), wrist hand (24 points), and coordination (6 points) and higher score indicate better upper limb movement function [4]. The FMA-UE is the most common scale for evaluating upper limb motor function after CIS. It is often used as a gold standard for testing the validity of other scales as well [26, 27]. The FMA-UE has excellent reliability and validity and is sensitive enough for clinical and research practice [28].

fMRI is a noninterventional imaging technique that uses magnetic resonance to measure changes in brain hemodynamics caused by neuronal activity as a reflection of the activation state of brain areas. For the observation methods, after the patients are ready, scanning will be performed on the whole brain of the patients. During resting-state scanning, patients will be instructed to relax, close their eyes, and avoid systematic thinking activities as much as possible. After resting-state scanning for 6 min, functional state scanning will be performed. The experimental task will be designed in blocks. There will be 10 trials for each task state (Fig. 3), and the time of each trial is 30 s. In addition, there are 10-s empty sweeps before each scan, so each scan is 5 min and 10 s. Once in place, the subjects will be put on noise-canceling earphones and receive instructions. Patients will be asked to try to imagine their fingers flexing when they hear the word “close.” When they hear the word “open,” they will be asked to try to imagine their fingers straightening. Each subject will receive task training in advance.

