### Data collection and statistical analysis

Therapists will collect the data using Case Report Forms. Two independent researchers will then input the data into the database. All analyses will be carried out under the guidance of independent data monitors to ensure the security and dependability of the data. About the dropped-out participants, their number and the reason for termination will be recorded, especially for adverse events. All enrolled patients will be included in the primary analysis conducted in accordance with the intention-to-treat (ITT) principle. The data will be analyzed by SPSS for Windows version 19.0. The statistical significance is defined as a two-sided *P* value of ≤ 0.05. The baseline characteristics will be reported as the means ± standard deviation (SD). For comparison of baseline materials, a chi-squared or Fisher’s exact test will be used for categorical variables, Student’s *t* test will be used for normally distributed data, and the Mann-Whitney *U* test will be used for non-normally distributed data. The scores of each rating scale and laboratory index before the intervention will be compared between the groups via Student’s *t* test or the Mann-Whitney *U* test. For the comparison within groups, the changes in the scores and indexes from baseline to endpoint will be assessed by a paired *t* test or the Wilcoxon rank-sum test. For the difference between groups, we will use Student’s *t* test or the Mann-Whitney *U* test. For the safety analysis, the adverse events will be listed and analyzed using a chi-squared or Fisher’s exact test. For participants who discontinue or deviate from intervention, listwise deletion or multiple imputation will be used.

The data of fMRI will be analyzed by professional technicians at the Shenzhen Advanced Institute.

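### The between-arm test of FMA-UE change does not condition on baseline FMA-UE and leaves the choice between a t test and a rank test open; a single ANCOVA would be as precise or more so, and would fix the method, at almost no cost.

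*Protocol article*

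**What the plan says.** All references are to the protocol article.

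- **Primary outcome** (Primary outcomes): it is expressed as a mean, "mean change in the scores on the FMA-UE from baseline to 4 weeks intervention and 12 weeks follow-up". fMRI is named alongside it.
- **Baseline is available** (Outcome measures): "FMA-UE, MAS, ARAT, ADL, and fMRI will be assessed before and after the treatment".
- **Between-arm test** (Data collection and statistical analysis): "For the difference between groups, we will use Student’s *t* test or the Mann-Whitney *U* test". No covariate is named, and no ANCOVA, regression or mixed model appears anywhere in the article.
- **Baseline scores**: apart from forming the change score and entering the within-group paired tests, they are compared between arms: "The scores of each rating scale and laboratory index before the intervention will be compared between the groups".
- **Choosing between the two tests**: a normality rule is given for baseline characteristics, where "the Mann-Whitney *U* test will be used for non-normally distributed data". It is not repeated for outcomes.
- **Level**: two-sided, 0.05.

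**The concern.** A patient's change is usually correlated with the starting score: those who start low tend to gain more on re-measurement. Subtracting baseline therefore removes a chance baseline difference between arms only when the regression slope of week-4 score on baseline is close to 1. Otherwise part of the difference stays in the comparison as avoidable noise. With 60 patients, precision is scarce.

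The second issue is the unqualified choice between two tests. The primary outcome is a mean change. The t test addresses it directly. The Mann-Whitney test compares distributions by rank and does not estimate a mean difference. If the data decide which test is reported, they also decide which quantity is reported.

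**Working it through.** **1. The plan's own figure.** The Sample size section assumes effective rates of 88.9% and 56.1%, alpha 0.05 and type II error 0.2. With unpooled variance:

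n = (1.960 + 0.842)² × [0.889 × 0.111 + 0.561 × 0.439] / (0.889 − 0.561)² = 7.85 × 0.3450 / 0.1076 = 25.17, so 26 per arm.

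The stated 26 is reproduced. It concerns a proportion, however, so it gives no power for mean FMA-UE change. The 80% used below is a hypothetical starting point.

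**2. Variance of ANCOVA relative to the change score.** The documents give no SD, no FMA-UE effect and no correlation, so r is varied. With s0 and s1 the baseline and week-4 SDs:

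ratio = s1²(1 − r²) / (s0² + s1² − 2·r·s0·s1)

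With s1 = s0 this becomes (1 − r²)/(2 − 2r) = (1 + r)/2. With s1 = 1.2·s0 it is 1.44(1 − r²)/(2.44 − 2.4r).

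| r | equal SDs | power by ANCOVA where the t test on change has 80% | s1 = 1.2·s0 |
|---|---|---|---|
| 0.6 | 0.80 | 87.9% | 0.9216/1.00 = 0.92 |
| 0.7 | 0.85 | 85.9% | 0.7344/0.76 = 0.97 |
| 0.8 | 0.90 | 83.9% | 0.5184/0.52 = 1.00 |
| 0.9 | 0.95 | 82.0% | 0.2736/0.28 = 0.98 |

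Power is from the noncentral t at 30 per arm, with one degree of freedom charged to ANCOVA. At 26 per arm, the required number before the dropout allowance, the powers agree to within about 0.1 percentage point. The last column reaches 1.00 near r = 0.8 because the slope 1.2r is then close to 1, and subtraction is already nearly the best adjustment.

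**3. Small-sample allowance.** Estimating the slope multiplies the ANCOVA variance by about 1 + 1/(2n − 4). At n = 30 per arm this is 1 + 1/56 = 1.018. The equal-SD ratios become about 0.81 to 0.97 (0.80 × 1.018 and 0.95 × 1.018). The worst entry in the last column becomes about 1.015 (0.997 × 1.018). The gain is thus slightly smaller than the table shows, and the largest loss in these scenarios is about 1.5% of variance.

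**4. Simulation check.** With 26 per arm, bivariate normal scores, equal SDs and 4,000 runs, power for t / Mann-Whitney / ANCOVA was 80/77/89% at r = 0.5, 79/76/84% at r = 0.7 and 80/77/81% at r = 0.9. This is the same pattern: a clear gain at moderate r and very little at 0.9.

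**5. Chance imbalance.** The 95% range of a baseline difference at 30 per arm is ±1.96 × √(2/30) = ±0.51 SD. With equal SDs, the change score leaves (1 − r) of it in the comparison: 0.4 × 0.51 = 0.20 SD at r = 0.6, and 0.2 × 0.51 = 0.10 SD at r = 0.8. If the SD were 15 points (an assumption), these would be 3.0 and 1.5 points. They sit at the edge of the range, so they are near-worst cases and not expected values.

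**6. Type I error under the open choice.** In null simulations, each test alone held 4.7% to 5.4%. Choosing by a Shapiro-Wilk check in each arm gave 4.7% to 5.1%. Running both tests and reporting the smaller p value gave roughly 6% to 7%, depending on the skewness of the data.

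**The case against.** The planned analysis does use baseline. It is subtracted from every patient's score and enters the within-group tests. A reader might infer that the plan ignores baseline altogether, and the text does not support that. What is absent is conditioning on it.

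The t test on change is unbiased under randomisation and holds its error rate. Chance imbalance is part of the sampling variability that its confidence interval already covers. A reader might infer that the primary estimate will be biased, and that does not follow either.

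The normality rule stands in the same paragraph, and the later alternative may be shorthand for it. Under that rule the simulated error rate stayed at 5%. A reader might infer that the protocol inflates type I error. That requires running both tests and picking the smaller p value, which the protocol does not describe.

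Finally, an analysis plan that is not shown may add adjusted models, and the gain could be close to nil. All of these points limit the size of the concern. They do not remove it: the article itself names unadjusted tests for the arm comparison. Even if the normality rule carries over, the data would select the test, and one of the two options does not estimate the mean change that defines the primary outcome.

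**Conclusion.** The point holds as a free improvement, not as an error that invalidates the comparison. The primary FMA-UE comparison is valid on average, but it is potentially less precise and less firmly specified than it needs to be.

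The size depends on quantities the documents do not give. With equal SDs, adjustment removes 20% (r = 0.6) to 5% (r = 0.9) of the variance. With a week-4 SD 1.2 times baseline it removes 8% to none. The small-sample allowance trims each figure by about two percentage points. In no scenario examined is there a material loss.

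The stated sample size is unaffected, because it rests on the effective rate. The between-arm tests of baseline scores are a minor matter: they test a null hypothesis that randomisation makes true, but no other analysis depends on them.

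**What to change.** - State one primary between-arm analysis for FMA-UE: ANCOVA of the week-4 score on arm, with baseline FMA-UE as covariate. Report the adjusted mean difference with its 95% CI whatever a normality check shows.
- This keeps the declared outcome. Using change as the response gives the same arm coefficient, because subtracting baseline from both sides only lowers the baseline slope by 1.
- Keep Mann-Whitney on change as a named sensitivity analysis.
- Use the same model, each with its own baseline, for FMA-UE at week 16 and for MAS, ARAT and ADL.
- Optionally, describe baseline scores by arm without testing them.

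**Cost:** a change of wording before the data are unblinded and one degree of freedom. It needs no new patients, visits or measurements, and the named software can fit the model.

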#### JTN group

In the control group, the acupuncture therapy will be the same as the treatment group’s.

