### Sample size

The sample size was calculated based on the effective rate of the treatment. Based on similar previous studies [30], we assumed the effective rate of 88.9% and 56.1% in the JTN+MT group and the control group, respectively. The PASS11.0 software was used to perform a power analysis to determine the sample size. Type-1 error was assumed at 0.05, type-2 error at 0.2. The required sample size was 26 subjects for each group. Considering a dropout rate of 15%, a total of 60 subjects needed to be enrolled (30 participants per group).

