### Adverse events and safety monitoring

Adverse events will be recorded and managed by researchers within 24 h. There will be at least one physician to evaluate and manage the adverse events at each center. Serious adverse and unexpected events will be reported to the Ethics Committee and other supervising departments. The subjects may leave the trial at their own discretion, or the physicians will determine whether the patient will continue or terminate the study. However, the patient will be followed up until they are in a stable condition following the adverse event.

The primary investigator will review all adverse events periodically, and the Ethics Committee and DMC will have access to the interim results. If necessary, a meeting will be held to reappraise the benefits and risk of this trial.

The possible adverse events related to acupuncture treatment include fainting during treatment, nausea, needle stuck, needle breakage, local hematoma, local infection, and viscera or peripheral nerve injury. Adverse events will be assessed based on the symptoms, frequency, and severity of the patients throughout the study. Patients who are intolerant to the treatment should be removed immediately from the trial.

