## Conclusion

In conclusion, the results of this study are expected to provide evidence on the efficacy and safety of JTN, to demonstrate and improve the clinical effect of JTN combined with MT in the treatment of upper limb dysfunction after CIS and to demonstrate the effect and safety of the therapy, thereby providing the scientific basis for its clinical promotion. Using fMRI brain functional imaging, the central brain mechanisms of these effects will be investigated, which will provide a strong evidence-based medical basis for further popularizing the application of JTN combined with MT.

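### The stated adverse-event test compares two arms that both receive acupuncture, so it cannot show that acupuncture is safe, and at 30 per arm it says little about mirror therapy

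*Protocol article*

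**What the plan says.** Under Data collection and statistical analysis, the Protocol article states: "For the safety analysis, the adverse events will be listed and analyzed using a chi-squared or Fisher’s exact test". The same section sets the criterion for all tests: "The statistical significance is defined as a two-sided" P value of at most 0.05. The text gives no assumed adverse event rate, margin or confidence interval for safety.

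For the control arm, the JTN group section says that "the acupuncture therapy will be the same as the treatment group’s". Mirror therapy is the only planned difference between the arms.

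Under Adverse events and safety monitoring, the only possible events named belong to needling: "The possible adverse events related to acupuncture treatment include fainting during treatment, nausea, needle stuck, needle breakage", followed by haematoma, infection and organ or nerve injury. That section also has events assessed by symptoms, frequency and severity throughout the study. Outcome measures adds laboratory safety tests before and after treatment.

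The trial was sized for efficacy: "The sample size was calculated based on the effective rate of the treatment". The abstract nevertheless aims to evaluate the safety of JTN. The Conclusion expects evidence on the safety of JTN and goes on: "to demonstrate the effect and safety of the therapy, thereby providing the scientific basis for its clinical promotion".

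**The concern.** There are two safety questions, and one test serves both.

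The first is whether JTN is safe. This is a question about an absolute rate. Both arms receive JTN, so its contribution to the event rate is the same in each and cancels from the comparison. Needling that harms 5% of patients and needling that harms 30% would both be expected to show no difference between arms. A larger trial would not cure this.

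The second is whether adding mirror therapy causes harm. The comparison does address that, but the trial was not sized for it and only very large differences would be detected.

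At stake is the safety half of the conclusion, which is offered as a basis for clinical promotion. A P value from this test could not carry that claim.

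**Working it through.** **Inputs.** 30 patients per arm and 60 in total (Sample size); two-sided P ≤ 0.05, with chi-squared or Fisher's test (Data collection and statistical analysis). The document gives no adverse event rates, so every rate below is an assumption, shown over a range.

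**The plan's own figure.** The Sample size section says "we assumed the effective rate of 88.9% and 56.1% in the JTN+MT group and the control group, respectively" and "Type-1 error was assumed at 0.05, type-2 error at 0.2". With unpooled variance and a two-sided test,

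n = (1.960 + 0.842)² × [0.889 × 0.111 + 0.561 × 0.439] / (0.889 − 0.561)² = 7.849 × (0.0987 + 0.2463) / 0.1076 = 25.2, rounded up to 26.

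The stated 26 per arm reproduces, and 26 × 1.15 = 29.9 gives the 30 enrolled. The calculation concerns efficacy only; no adverse event rate enters it.

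**Question 1: safety of JTN.** If the true event rate is the same in both arms, the expected difference is zero at any rate. Exact enumeration, summing the probabilities of all outcomes with P ≤ 0.05, gives the chance that Fisher's test rejects at 30 per arm:

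| Rate in both arms (assumed) | Fisher rejects |
|---|---|
| 5% | 0.15% |
| 10% | 0.9% |
| 30% | 2.6% |

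Non-significance is nearly certain whether the shared rate is low or high, so the P value cannot separate safe from harmful needling.

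**Question 2: added harm from mirror therapy.** Exact power at 30 per arm:

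| Rates (assumed) | Fisher | Uncorrected chi-squared |
|---|---|---|
| 5% vs 10% | 1.9% | 11% |
| 10% vs 20% | 9.6% | 19% |
| 5% vs 20% | 24% | 45% |

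With no events in one arm, Fisher gives P = 0.052 for 0 vs 5 and P = 0.024 for 0 vs 6. Uncorrected chi-squared is already significant at 0 vs 4 (P = 0.038). At 0 vs 5 the expected event count is 2.5 per arm, and with counts that small Fisher is the usual choice. For scale, 80% power by the normal approximation would need 435 per arm for 5% vs 10% and 199 per arm for 10% vs 20%.

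**What estimation would show.** With zero events among n patients, the exact two-sided 95% upper limit is 1 − 0.025^(1/n):

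- n = 30: 1 − 0.025^(1/30) = 11.6%
- n = 60: 1 − 0.025^(1/60) = 6.0%

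With 3/30 in each arm, the Newcombe 95% interval for the risk difference is −17 to +17 percentage points. These intervals show directly what the trial can and cannot exclude; a P value does not.

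**The case against.** The strongest reply is that the plan does not rest safety on this test. Events are listed and assessed by frequency and severity, physicians evaluate them, the investigator reviews them, and the Ethics Committee and data monitoring committee can see interim results. The laboratory safety indexes are compared as well. A harmful needling regimen would show in the listing whatever the P value. This stands, and it limits the point: the test is the stated inferential analysis of adverse events, not the whole of the safety assessment.

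Two stronger readings are tempting, and the document supports neither. A reader might infer that P > 0.05 will be taken as proof of safety. No section states such a rule, and other wording is milder: the abstract's discussion says only that the study may help to identify safety. A reader might also infer that only needling events will be tested. The test applies to the adverse events recorded, and the list of possible events is illustrative and labelled as related to acupuncture, so events from mirror training are not excluded.

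It can also be said that needling events need not be equal in the two arms. The description of the combined arm leaves unclear whether mirror training overlaps with the time the needles are in place. This stands as a reason to report needling events by arm as well as pooled. It does not make the comparison a measure of the safety of JTN.

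Finally, intervals and event classification are often left to an analysis plan, which is not shown. Their absence alone would be no finding. The point here is that the method the article does state does not match the claim it does make.

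**Conclusion.** The point holds as a modest mismatch between a stated analysis and a stated claim. For JTN it is a matter of design and needs no assumed rate: a comparison of two arms that both receive JTN does not estimate its risk. For mirror therapy it is a matter of size. Power to detect a doubling from a base of 5% or 10% is about 2% to 10% with Fisher and 11% to 19% with uncorrected chi-squared. Those figures rest on assumed rates and on all 30 patients per arm being analysed; fewer would lower them.

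The primary efficacy analysis is not affected. What changes is how much the trial can say about safety: it can describe adverse event rates with wide intervals, and it cannot demonstrate safety.

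**What to change.** In Data collection and statistical analysis, make estimation the safety analysis:

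- the proportion of patients with at least one acupuncture-related event, by arm and pooled over both arms, each with an exact 95% confidence interval;
- the proportion with any adverse event by arm, and the risk difference with a 95% confidence interval, as the estimate for adding mirror therapy;
- a sentence stating that a non-significant test is not evidence of safety. The test may stay as a supplement.

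The first item needs each event classed by cause. The case report form is not shown, so whether it already records this is unknown.

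In the Conclusion, replace the aim of demonstrating safety with wording that limits the safety claim to describing adverse event rates in the two arms.

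The cost is a few lines of text and a short analysis, with no change to treatment, visits or sample size. The downside for the sponsor is a less favourable safety claim: even with no acupuncture-related event in 60 patients, a rate of up to 6.0% would remain compatible with the data.

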#### Concomitant treatments

The patients in two groups will be treated with basic medications in the meantime. The patients in two groups will be treated with basic medications according to guidelines for clinical management of cerebrovascular disorders [25] to control blood pressure: individual treatment is adopted to stabilize blood pressure below 135/85 mmHg or within the normal range, control blood sugar and lipid, and prevent platelet aggregation.

The patients in the two groups will be provided with instructions to discourage them from receiving any additional specific complementary treatments related to upper limb dysfunction after CI throughout the trial, including abdominal acupuncture, fire acupuncture, floating acupuncture, and other acupuncture therapies, moxibustion, herbal medicine, massage, etc. If a patient needs other prescription medication, the relevant information will be recorded in the Case Report Form for that patient. The data will be assessed by two blinded researchers, to ensure whether be included.

For follow-up, all participants will participate in a 12-week follow-up after 4 weeks intervention. At the end of a 12-week follow-up period, participants will be referred for clinical evaluation to assess their functional status, including Fugl–Meyer Assessment for Upper Extremity (FMA-UE), motor assessment scale (MAS), action research arm test (ARAT), and activities of daily living (ADL) scale.

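### The protocol promises an ITT primary analysis of all enrolled patients but leaves open deleting those who discontinue or deviate, so the primary analysis can become a completer or per-protocol analysis

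*Protocol article*

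**What the plan says.** The section on data collection and statistical analysis sets the primary population: "All enrolled patients will be included in the primary analysis conducted in accordance with the intention-to-treat (ITT) principle". The same paragraph ends: "For participants who discontinue or deviate from intervention, listwise deletion or multiple imputation will be used". It does not say how the choice between the two methods is made, or whether either is primary or a sensitivity analysis.

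The section on concomitant treatments covers drugs outside the basic regimen: "If a patient needs other prescription medication, the relevant information will be recorded in the Case Report Form for that patient". It continues: "The data will be assessed by two blinded researchers, to ensure whether be included". No criterion for inclusion is given.

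The section on adverse events and safety monitoring states: "Patients who are intolerant to the treatment should be removed immediately from the trial". It promises follow-up after an adverse event until the patient's condition is stable. The section on concomitant treatments, however, has every participant attend a 12-week follow-up with FMA-UE and the other scales.

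**The concern.** Listwise deletion of patients who stop or deviate removes enrolled patients from the analysis, so it cannot stand beside the promise to analyse all of them. The trigger makes this worse. It is what happened to the treatment, not whether an outcome is missing. Read literally, a patient who missed sessions but has a complete week-4 FMA-UE could be deleted.

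Discontinuation, deviation and the need for other medication all arise after randomisation. Patients know whether they receive mirror therapy, so these events may differ by arm. If they are also related to recovery, deletion gives up the comparability that randomisation provided. Two methods that can give different answers, with no rule between them, also let the choice be made after the data are seen.

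**Working it through.** **1. The two sentences side by side.** ITT sentence: all enrolled patients are in the primary analysis. Handling sentence: those who discontinue or deviate are deleted or imputed. Under deletion the ITT sentence is false for every such patient. Under imputation both can hold, provided that only missing values are imputed. The text does not say which applies.

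**2. The plan's own figures.** The sample size section states: "we assumed the effective rate of 88.9% and 56.1% in the JTN+MT group and the control group, respectively" and "Type-1 error was assumed at 0.05, type-2 error at 0.2". The test is two-sided according to the statistical section. With the unpooled normal formula:

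n = (1.960 + 0.842)² × (0.889 × 0.111 + 0.561 × 0.439) / (0.889 − 0.561)² = 7.849 × 0.34496 / 0.10758 = 25.2, so 26 per arm.

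The stated 26 reproduces. Exact power of the chi-squared test is 80.1% at 26 per arm and 84.2% at 30. The planned 15% loss is 0.15 × 60 = 9 patients and leaves 0.85 × 30 = 25.5 per arm, about what the design requires. Deletion within the planned loss therefore costs little precision against the design. The issue is bias.

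**3. Bias on the effective-rate scale (assumed figures).** Let true success be p = 0.561 in both arms, so there is no effect, and let only failures be deleted. If a fraction q of an arm is deleted, the success rate among those left is p / (1 − q).

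| Deleted, arm A / arm B | Rate in A | Rate in B | Spurious difference |
|---|---|---|---|
| 15% / 15% | 0.561/0.85 = 66.0% | 66.0% | 0 |
| 20% / 10% | 0.561/0.80 = 70.1% | 0.561/0.90 = 62.3% | 7.8 points |
| 25% / 5% | 0.561/0.75 = 74.8% | 0.561/0.95 = 59.1% | 15.7 points |

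Each row deletes 9 of 60 in total (for example 6 + 3 in the second), which equals the planned 15%. The arm that loses more failures looks better, so the error can favour either arm. Deleting failures only is the extreme case. If deletion is unrelated to outcome, both arms stay at 56.1%.

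**4. Bias on a continuous score (assumed figures).** The outcome section makes mean FMA-UE change primary, so the same question was simulated for a mean: no true effect, 30 per arm, t test at 0.05, 4,000 runs, with low responders more likely to be deleted. The strength of that link is the correlation between outcome and the tendency to be deleted.

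| Correlation | 15% / 15%: type I error | 20% / 10%: bias, type I error | 25% / 5%: bias, type I error |
|---|---|---|---|
| 0 | 0.054 | 0.00 SD, 0.053 | 0.00 SD, 0.048 |
| 0.3 | 0.048 | 0.05 SD, 0.055 | 0.10 SD, 0.065 |
| 0.5 | 0.054 | 0.08 SD, 0.071 | 0.16 SD, 0.088 |
| 1 | 0.054 | 0.15 SD, 0.096 | 0.32 SD, 0.259 |

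The simulation error of a rate near 0.05 is √(0.05 × 0.95 / 4000) = 0.003. Harm needs both conditions, unequal deletion and a link with outcome. Without either one, type I error stays at about 0.05.

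**The case against.** Multiple imputation is offered beside deletion and fits the ITT promise. The handling sentence does not say which analysis it governs, so deletion might be meant for a secondary one. It may also be loose wording for missing data that follow from stopping treatment. This stands in part: a reader might infer that the plan has committed itself to a completer analysis, and the text does not support that. It only permits one. Likewise, nothing says that imputation would overwrite observed values; the trigger merely fails to rule it out.

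The medication review is done by blinded researchers, which limits selective exclusion by arm. The sentence is also unclear on whether the patient, the outcome data or the medication record is to be included. Both points stand, so this is not a settled exclusion rule. Blinding does not, however, supply the missing criterion, nor does it keep an event after randomisation balanced between arms.

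A reader might also argue that mirror therapy adds 30 minutes a day and so raises loss in the combined arm. The intervention section does not settle this. It describes a 30-minute course during which mirror therapy is given, but also supine needling and seated mirror training. Unequal loss is possible, not shown.

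Finally, a reader might infer a large loss of power by counting all dropouts as failures: 0.85 × 88.9% = 75.6% against 0.85 × 56.1% = 47.7%, with exact power of 60.8% at 30 per arm compared with 84.2%. That does not measure this defect. Neither ITT nor the fix below requires dropouts to be scored as failures. Also, if the higher rates are those of completers, they belong with about 25 to 26 per arm, where power is about 78% to 80%, not 84.2%.

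**Conclusion.** The contradiction holds and lies in the text shown; it is not detail left to an analysis plan. The protocol promises ITT on all enrolled patients, yet allows patients to be deleted for non-adherence. It has no rule for choosing the alternative, and it adds a criterion-free inclusion decision for patients on other medication. The primary analysis can therefore become a completer or per-protocol analysis.

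The size depends on assumptions that the documents cannot settle. With 9 of 60 deleted, the spurious difference runs from 0 (balanced, or unrelated to outcome) through 7.8 points (20% against 10%, failures only) to 15.7 points (25% against 5%, failures only). For a mean score, type I error runs from about 0.05 to 0.26 over the settings tried. These are illustrations, not forecasts. The point should be corrected because the stated rules conflict on the primary comparison and the correction is cheap.

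**What to change.** In the statistical section, state that every randomised patient is analysed in the assigned arm with all observed FMA-UE values, whatever the adherence or other medication. Name one method, only for values that are actually missing; for example, multiple imputation by arm using baseline and available follow-up FMA-UE. Move listwise deletion to a labelled sensitivity analysis.

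In the section on concomitant treatments, say what the two blinded researchers decide on and by which criterion, and confine any resulting exclusion to a labelled sensitivity or per-protocol analysis.

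Reconcile the removal of intolerant patients from the trial with ITT and with the 12-week follow-up of all participants. The point to settle is whether the outcome assessments already scheduled continue after treatment stops. No treatment-stopping rule needs to change for this.

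The cost is minor rewording in three sections, a little more analysis work, and continued outcome collection at visits that are already scheduled.
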